## Abstract

**Background:**

The demand for mental health care, particularly for depression and anxiety, is 3-fold greater among patients receiving oncologic and palliative care than for the general population. This population faces unique barriers, making them more susceptible to mental health challenges. Various forms of psychotherapy have been deemed effective in addressing mental health challenges in this population, including supportive psychotherapy, cognitive behavioral therapy, problem-based therapy, and mindfulness; however, their access to traditional face-to-face psychotherapy resources is limited owing to their immunocompromised status, making frequent hospital visits dangerous. Additionally, patients can face hospital fatigue from numerous appointments and investigations or may live in remote areas, which makes commutes both physically and financially challenging. Web-based psychotherapy is a promising solution to address these accessibility barriers. Moreover, web-based psychotherapy has been proven effective in addressing depression and anxiety in other populations and may be implementable among patients receiving oncologic and palliative care.

**Objective:**

The study will investigate the feasibility and effectiveness of web-based psychotherapy among patients receiving oncologic and palliative care, who have comorbid depression or anxiety. We hypothesized that this program will be a viable and efficacious treatment modality compared to current treatment modalities in addressing depression and anxiety symptoms in this population.

**Methods:**

Participants (n=60) with depression or anxiety will be recruited from oncology and palliative care settings in Kingston (Ontario, Canada). Participants will be randomly allocated to receive either 8 weeks of web-based psychotherapy plus treatment as usual (treatment arm) or treatment as usual exclusively (control arm). The web-based psychotherapy program will incorporate cognitive behavioral therapy, mindfulness, and problem-solving skills, and homework assignments with personalized feedback from a therapist. All web-based programs will be delivered through a secure platform specifically designed for web-based psychotherapy delivery. To evaluate treatment efficacy, all participants will complete standardized symptomology questionnaires at baseline, midpoint (week 4), and posttreatment.

**Results:**

The study received ethics approval in February 2021 and began recruiting participants in April 2021. Participant recruitment has been conducted through social media advertisements, physical advertisements, and physician referrals. To date, 11 participants (treatment, n=5; control, n=4; dropout, n=2) have been recruited. Data collection and analysis are expected to conclude by December 2021 and January 2022, respectively. Linear regression (for continuous outcomes) will be conducted with interpretive qualitative methods.

**Conclusions:**

Our findings can be incorporated into clinical policy and help develop more accessible mental health treatment options for patients receiving oncologic and palliative care. Asynchronous and web-based psychotherapy delivery is a more accessible, scalable, and financially feasible treatment that could have major implications on the health care system.

**Trial Registration:**

ClinicalTrials.gov NCT04664270; https://clinicaltrials.gov/ct2/show/NCT04664270

**International Registered Report Identifier (IRRID):**

DERR1-10.2196/30735

## Introduction

### Background and Rationale

Common psychiatric disorders are highly prevalent among patients receiving oncologic and palliative care, with approximately 40% of these patients showing symptoms of depression and anxiety [1]. This alarming prevalence is 3-fold that in the general population, with mood and anxiety disorders being the most common psychiatric challenges among these patients [1,2]. Additionally, the prevalence of this psychiatric morbidity is further elevated in those with more advanced and incurable diseases [3]. Despite this high comorbidity of mood and anxiety disorders in patients with cancer, these disorders are massively underdiagnosed and often remain untreated [4]. In addition to the increased burden these mental health challenges have on individual patients, the cost of care for their underlying medical problem is almost twice as high in the presence of mental health comorbidities [5]. Therefore, addressing these mental health challenges must be of top priority to help patients, and is necessary to limit the costs of these diseases on public health.

Both medication and psychotherapy are effective in treating mood and anxiety disorders in patients receiving oncologic and palliative care. However, considering the complex pharmacological management of cancers and the possibility of medication interactions, psychotherapy may be a better choice for managing mental health disorders in these patient groups [6]. Different studies have shown the efficacy of psychotherapy in patients with cancer to control mental health comorbidities, and it has been shown that in addition to mental health symptoms, supplementation of psychotherapy to the normal course of treatment can improve medical outcomes as well [7,8]. However, while highly effective, the traditional face-to-face method of delivering psychotherapy has significant limitations that are magnified among patients receiving oncologic care. The duration of treatment, access to treatment, access to qualified personnel, and specific evidence-based tools are barriers that can limit patients receiving oncologic and palliative care from accessing the care they need and deserve. To address these challenges, 1 potential solution is to offer web-based, asynchronous therapy instead of or in addition to traditional live, in-person treatment.

In recent years, web-based psychotherapy has emerged as a promising solution to address the inaccessibility and inefficiency issues of in-person treatment. More specifically, web-based delivery of cognitive behavioral therapy (e-CBT) has been shown to decrease depressive symptoms and sustain beneficial effects [9-12]. Being available anywhere, at any time, and in any language, e-CBT can make mental health care more accessible geographically, temporally, and culturally. Furthermore, by delivering psychotherapy on the internet, clinicians can sustain a cost-effective and time-efficient practice. This method of delivery can also increase treatment flexibility and improve treatment adherence among patients.

Addressing the psychological needs of patients receiving oncologic and palliative care can significantly decrease the burden of disease and their overall suffering. Considering previous reports of the successful outcomes of e-CBT for various mental health challenges [9,13,14], we believe that e-CBT can be successfully implemented in an oncology and palliative care setting as well.

### Objectives

This study aims to establish a web-based psychotherapy clinic at an academic center for the management of depression and anxiety in patients receiving oncologic and palliative care, specifically to meet the needs of this underserved specialized population. If successful, this approach could increase the capacity and quality of mental health among patients with cancer who receive palliative care and could also, directly and indirectly, minimize the financial burden of these diseases on the public health system. We hypothesized that this e-CBT program can effectively address depressive and anxiety symptoms in patients receiving oncologic and palliative care. This study will aim to address the following research questions:

Is this e-CBT and mindfulness program a suitable therapeutic modality to address the psychological needs of patients receiving oncologic and palliative care?Is the web-based delivery of this psychotherapy program through a secure platform an effective solution to meet the increased demands of patients receiving oncologic and palliative care?

## Methods

### Study Design

This study will employ an open-label randomized controlled trial design to investigate the efficacy of a web-based psychotherapy program in treating anxiety and depressive symptoms in patients receiving oncologic and palliative care. Participants will be randomly allocated to receive either the web-based psychotherapy program or treatment as usual (TAU) for 8 weeks. This study has been registered on ClinicalTrials.gov (protocol# NCT04666974).

### Participants

Patients (n=60) diagnosed with depressive or anxiety disorders due to another medical condition in the context of oncologic or palliative care will be recruited through referrals from the Kingston Health Sciences Centre (including the cancer center), Providence Care Hospital, family physicians, other health care providers, and self-referrals in Kingston (Ontario, Canada). After consenting to take part in the study, a complete assessment will be performed by one of the psychiatrists on the team to confirm the diagnosis. Inclusion criteria are an age of 18-55 years at the start of the study; a diagnosis of depression or anxiety secondary to a general medical condition (in the context of oncologic or palliative care conditions), using the Diagnostic and Statistical Manual of Mental Disorders, 5th edition, by one of the psychiatrists on the team; competence to consent and participate in the study; ability to speak and read in English; and consistent and reliable access to the internet. Exclusion criteria are having acute hypomanic or manic episodes, acute psychosis, severe alcohol or substance use disorder, active suicidal or homicidal ideation, or currently receiving or having received CBT in the past year. Participants will then be randomly assigned to two groups: TAU control group (ie, medication, psychiatric consultation, referrals to in-person activities or groups, etc) or the e-CBT (e-CBT + mindfulness + problem solving + TAU) treatment group. Participant allocation will be equally stratified (e-CBT, n=30; TAU, n=30).

### Procedures

Patients in the e-CBT group will receive an 8-week web-based program that includes CBT in combination with mindfulness and problem-based therapy in addition to TAU. The content of this program will be customized to reflect challenges that patients receiving oncologic and palliative care face through the course of their treatment, and developed to contain interactive and engaging therapy modules. All web-based sessions and interactions will occur through the Online Psychotherapy Tool (OPTT), a secure internet-based platform. Through this platform, the predesigned therapy modules will be assigned to the patients, which will be accessible to them at any time throughout the week. Each module will consist of approximately 30 slides, which take an average of 50 minutes to complete. Each weekly module will highlight a different topic and includes general information, an overview of skills, and homework to be completed within that week. This homework can be directly submitted through the OPTT to the clinician who will then provide personalized feedback to the patient. The average time spent per week by a clinician with a particular patient is approximately 15 minutes. Patients in the control group will receive TAU for the first 8 weeks; if still significantly symptomatic (<50% response to treatment from baseline), they will then be offered the 8-week e-CBT program.

### Therapist Training

All therapists have experience in psychotherapy delivery and are trained by a psychiatrist in our group. Additionally, all therapists learn the specifics of the modules covered in treatment, along with the standard care pathway. The therapists in our group include a combination of medical graduates and residents, graduate students, and trained research assistants. Before working with any patients, therapists will provide practice feedback on simulated sessions, which will be analyzed by the psychiatrists in our group to ensure that the quality of care is adequate. All therapists will be supervised by the principal investigator, who is an expert in delivering web-based psychotherapy. Moreover, feedback on homework will only be sent to patients after it is read, edited, and approved by the supervisor. Any issues regarding OPTT will be handled through OPTT technical support, which can be accessed at any time.

### Ethics and Data Privacy

All procedures have been approved by the Queen’s University Health Sciences and Affiliated Teaching Hospitals Research Ethics Board (file# 6031471). For privacy purposes, participants will only be identifiable by an identification number on the OPTT, and hard copies of the consent forms with participants’ identities will be stored securely on site and destroyed 5 years after study completion. Participant data are only accessible by the care providers who are directly assigned to that participant, and only anonymized data are provided to the analysis team. Participants have the option to withdraw from the study at any point and request for their data to be removed from the analysis. However, since the collected data are considered a medical record, they will not be permanently deleted for 10 years after treatment.

The web-based platform used in this study (OPTT) complies with the Health Insurance Portability and Accountability Act, Personal Information Protection and Electronic Documents Act, and Service Organization Control-2 policy. Additionally, all servers and databases are hosted in the Amazon Web Service Canada cloud infrastructure, which is managed by Medstack, to ensure that all provincial and federal privacy and security regulations are met. The OPTT does not collect any identifiable personal information or IP addresses for privacy purposes. The OPTT only collects anonymized metadata to improve its service quality and provide advanced analytics to the clinician team. The OPTT encrypts all data, and no employee has direct access to the participant data. All encrypted backups are maintained in the S3 storage, which is dedicated to Queen’s University, Kingston.

### Outcome Evaluation

The primary outcome measure will be the progression or regression of our participants’ mental health symptoms. Outcome measures will include the scores of the following standardized questionnaires: Functional Assessment of Cancer Therapy-General, 9-item Patient Health Questionnaire, 7-item Generalized Anxiety Disorder, 14-item Resilience Scale, and the Quality of Life and Satisfaction Questionnaire. Assessments will be completed upon study entry and after weeks 4 and 8 of the program. Other behavioral data regarding patients’ interaction and engagement with their therapy (ie, number of logins per day and amount of time spent on each session) will be collected directly through the OPTT to obtain further insight. We hypothesized that the level of patient engagement may have predictive power in therapy outcomes.

The anticipated quantitative outcomes include a progression of questionnaire scores, high frequency of logins, and high frequency of logins during nonbusiness hours. The anticipated qualitative outcome is positive feedback from participants receiving e-CBT and health care providers.

### Data Analysis

Initially, all data will be examined for missing, nonsensical, and outlying variables. Missing data will be treated as missing and not imputed (ie, will be analyzed on a per-protocol basis). Given the likelihood of participant dropout or withdrawal, participants have been purposely oversampled to obtain meaningful and statistically significant results at the end of the study. Based on previous experience with CBT and e-CBT in similar patient populations, the anticipated dropout is up to 30% by the end of the phases. However, the remaining individuals will be able to provide significant information regarding changes in their symptoms. Given that several outcomes will be considered, it is difficult to calculate a single sample size or provide a specific power calculation. However, using the 9-item Patient Health Questionnaire as an example, as it is common to all participants, a 30% change is considered clinically significant. Therefore, a sample size of 20 participants in each arm of the study would be sufficient for obtaining significant results with *P*=.05 and a power of 0.95.

Baseline and demographic data from individuals who drop out will be compared to those who finish identifying any fundamental differences between completers and noncompleters. Linear regression models will be used to compare treatment and control outcomes while controlling for demographic variables such as age and gender.

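### The only stated treatment comparison is per-protocol, apparently in those who remain, with up to 30% dropout expected; if dropout is outcome-related and differs by arm, this can favour e-CBT

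*Protocol article*

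**What the plan says.** All of this is in the protocol article.

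- **Analysis rule (Data Analysis).** "Missing data will be treated as missing and not imputed (ie, will be analyzed on a per-protocol basis".
- **Expected loss (Data Analysis).** "the anticipated dropout is up to 30% by the end of the phases". The article relies on those who stay: "the remaining individuals will be able to provide significant information regarding changes in their symptoms".
- **Use made of dropouts (Data Analysis).** "Baseline and demographic data from individuals who drop out will be compared to those who finish".
- **Model (Data Analysis).** "Linear regression models will be used to compare treatment and control outcomes while controlling for demographic variables such as age and gender". No intention-to-treat set, repeated-measures model or missing-data sensitivity analysis is named.
- **Data collected (Outcome Evaluation).** "Assessments will be completed upon study entry and after weeks 4 and 8 of the program".
- **Design (Study Design, Participants, Procedures).** The trial is open-label with 30 participants per arm. Only e-CBT carries weekly modules of about 50 minutes with homework. TAU participants who remain symptomatic are offered e-CBT after week 8.
- **Data removal (Ethics and Data Privacy).** A participant may withdraw and ask for their data to be taken out of the analysis.

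**The concern.** Not imputing is not the fault. A likelihood-based analysis of everyone randomised would not impute either. The fault is that the article equates not imputing with a per-protocol analysis and offers nothing else. The rule is stated outright, so it has not simply been left to a fuller document.

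Randomisation makes the two arms comparable at entry. A comparison of those who remain keeps that property only if leaving has the same relation to outcome in both arms, or none. Here there are reasons for a difference. The e-CBT arm has a weekly workload that TAU lacks. TAU participants have the later offer of e-CBT as a reason to stay. Illness-related loss is also likely in this population.

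If people who do badly leave e-CBT more readily, the remaining e-CBT group looks better than the group randomised. The article's Conclusions and Discussion aim the findings at clinical policy, for which the relevant effect is the one in everyone offered the programme.

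**Working it through.** **1. The plan's own allowance for dropout.** The Data Analysis section asks for 20 per arm and allows 30% loss. 20 / (1 - 0.30) = 28.6, so 29 per arm are needed and 30 are planned. 30 × 0.70 = 21 completers per arm. The oversampling is adequate for the number of completers. It does not make the completers of the two arms comparable.

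**2. The completer/noncompleter check.** At 30% loss, 60 × 0.30 = 18 noncompleters are set against 42 completers. The check uses baseline and demographic data only, is not described as being made by arm, and changes no estimate.

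**3. Bias under no true effect, by formula.** Assumed, not in the documents: a normal outcome in which higher is worse; correlation ρ of 0.3 to 0.7 between the tendency to drop out and a worse week-8 score; and the dropout fraction d in each arm. Those who remain in an arm have a mean shifted by -ρ·φ(c)/(1 - d) SD, with c = z(1 - d).

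| d | ρ = 0.3 | ρ = 0.5 | ρ = 0.7 |
|---|---|---|---|
| 0.30 | -0.149 | -0.248 | -0.348 |
| 0.10 | -0.058 | -0.097 | -0.136 |

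The bias in the arm difference is the e-CBT shift minus the TAU shift. The type I error comes from simulated completer t-tests (30 randomised per arm, 4000 runs, two-sided 5%).

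| Dropout e-CBT / TAU | Mechanism | Bias in SD (ρ = 0.3, 0.5, 0.7) | Type I error |
|---|---|---|---|
| 30% / 30% | same in both arms | about 0 | about 0.05 |
| 30% / 10% | same in both arms | -0.09, -0.15, -0.21 | 0.06, 0.08, 0.12 |
| 30% / 30% | outcome-related in e-CBT only | -0.15, -0.25, -0.35 | 0.07, 0.12, 0.21 |

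For example, the second row at ρ = 0.5 is -0.248 - (-0.097) = -0.151 SD.

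**4. Bias on the PHQ-9 scale, with week-4 scores.** Assumed: means 15, 13 and 12 at baseline, week 4 and week 8; SD 5; correlations 0.5 (baseline with week 4), 0.4 (baseline with week 8) and 0.7 (week 4 with week 8); 30 per arm; no true effect. Dropout in e-CBT is about 31% and more likely with a high week-4 score, at three strengths. TAU dropout is 10% at random. Every dropout is given a week-4 score.

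| Analysis | Bias (points) | Rejection at 5% |
|---|---|---|
| Completers, unadjusted | -0.9 to -1.6 | about 9-20% |
| Completers, adjusted for baseline | -0.65 to -1.2 | about 7-15% |
| Likelihood, all data | about 0 | 4.5-4.9% |

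With the same week-4-related dropout of about 30% in both arms, the completer bias is about 0 and rejection is 4.5-5.2%. If dropout depends instead on the unseen week-8 score, the likelihood analysis is itself biased by -0.7 to -1.3 points and rejects in 8-16%.

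**5. Power.** With equal random 30% dropout and a true 4-point effect, power is about 0.72 for unadjusted completers, 0.77 for completers adjusted for baseline and 0.82 using all data. Of the gain of 0.82 - 0.72 = 0.10, baseline adjustment gives 0.77 - 0.72 = 0.05. The other 0.05 comes from using the partial data.

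**The case against.** The strongest reply is that the bias is conditional. The article gives no dropout rate by arm, and with the same rate and mechanism in both arms the bias under no effect is about 0. That stands, so the size must be given as a range that includes zero.

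Three stronger readings are tempting, and the documents do not support them.

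- **Week-4 scores of dropouts are thrown away.** The text does not say so, nor does it name week 8 as the sole endpoint. The per-protocol label and the reliance on those who remain make this the likely reading, and no named method uses those scores for dropouts. It is still an inference.
- **Dissatisfied participants vanish from e-CBT alone.** Nothing in the article shows this. Step 4 assumes it, with 31% symptom-related dropout in one arm and 10% random dropout in the other.
- **The recruitment count already hides dropout by arm.** The abstract reports "11 participants (treatment, n=5; control, n=4; dropout, n=2) have been recruited", and 5 + 4 + 2 = 11. In the Participants section, consent comes before the diagnostic assessment and before allocation, so the two dropouts may never have been randomised.

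It is also fair to say that a repeated-measures model is no complete cure. It removes the bias only when dropout depends on observed data, and people who leave before week 4 contribute less to it. Half of its power advantage here is baseline adjustment. These points shape the remedy. They do not defend a per-protocol analysis as the only comparison.

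**Conclusion.** The concern holds in conditional form. The plan makes a per-protocol analysis, apparently of those who remain, its only stated treatment comparison while expecting up to 30% loss. Neither stated safeguard corrects selection. If dropout is related to outcome and differs between arms in rate or mechanism, the estimate can be biased towards e-CBT.

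On an assumed PHQ-9 SD of 5 and no true effect, the bias lies between about 0 and about -1.6 points (1.6 / 5 = 0.32 SD), with rejection between about 5% and 20% at a nominal 5%. The upper end needs dropout that differs markedly by arm. The SD, correlations and dropout by arm are assumptions, because the article gives none of them. The documents do not show that a spurious benefit will occur.

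**What to change.** Replace both the per-protocol sentence and the linear-regression sentence in Data Analysis, so that two primary models do not stand side by side:

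> The primary analysis includes all randomised participants in the arm assigned, regardless of adherence, except data withdrawn at the participant's request, which are counted by arm. A likelihood-based repeated-measures model of week-4 and week-8 scores has arm, visit, arm-by-visit, baseline score, age and gender; the week-8 arm difference is the estimate.

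Baseline enters once, as a covariate. In addition:

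- Keep the per-protocol or completer analysis as a labelled sensitivity analysis.
- Add a missing-not-at-random sensitivity analysis, for example a delta shift for dropouts, because of the residual bias in step 4.
- Report dropout by randomised arm, with losses before randomisation shown separately.
- Where participants agree, send the existing week-4 and week-8 questionnaires to those who stop the programme. The article does not describe this, so it is new follow-up.

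The cost is revised wording, a little more modelling and modest follow-up effort. No additional patients are needed. The estimated effect may be smaller than the one in completers.

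### The trial is sized on PHQ-9 although anxiety-only patients are eligible, and the stated regression names neither index diagnosis nor baseline score, so the 0.95 power depends on an unstated diagnostic mix

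*Protocol article*

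**What the plan says.** Protocol article, Participants: entry requires "a diagnosis of depression or anxiety secondary to a general medical condition", confirmed by a study psychiatrist. No minimum score on any scale is stated, so a patient with anxiety and few depressive symptoms can enter.

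Outcome Evaluation: the primary outcome is mental health symptoms in general. The scales listed include "9-item Patient Health Questionnaire, 7-item Generalized Anxiety Disorder" and three others, completed at entry and after weeks 4 and 8. No single scale is named as primary.

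Data Analysis: the sample size is reasoned "using the 9-item Patient Health Questionnaire as an example, as it is common to all participants". The effect is stated as "a 30% change is considered clinically significant", and the conclusion is that "a sample size of 20 participants in each arm of the study would be sufficient for obtaining significant results", at P=.05 and power 0.95. No baseline mean, SD or diagnostic mix is given. Dropout is put this way: "the anticipated dropout is up to 30% by the end of the phases". Treatment and control are then to be compared by linear regression. Age and gender are named as examples of the demographic covariates; baseline score and diagnosis are not named.

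**The concern.** That everyone completes the PHQ-9 does not make it a suitable basis for sizing, because the same is true of the other four scales. What sizing needs is that the assumed effect and SD describe the patients enrolled. The eligibility rule does not secure this, since depressive symptoms may be slight in anxiety-only entrants. A proportional improvement from a low baseline is a small number of points, so the mean difference over the whole sample is smaller than in depressed patients.

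Differences in level between the two diagnostic groups also add spread to week-8 scores unless the model removes them. The named covariates do not. At stake is whether 20 evaluable patients per arm come near the power claimed, and whether the analysis uses information already recorded on each patient.

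**Working it through.** **1. What the plan's figure implies.** Inputs from Data Analysis: 20 per arm, alpha 0.05 (two-sided assumed), power 0.95. By normal approximation d = (1.960 + 1.645) × √(2/20) = 1.14; by noncentral t, d = 1.17. The figure of 20 cannot be rebuilt from the plan's own inputs, because a 30% change without a baseline mean and SD does not give d. The dropout step is consistent: 30 × 0.7 = 21 evaluable per arm.

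**2. Illustration of the mix.** These inputs are assumptions and are not in the documents: depressed baseline 15, anxiety-only baseline Ma = 6 or 8, within-group SD 5, a 30% effect in every treated patient, no change in controls, and an anxiety-only share f of 20-50%.

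- Mean effect: (1−f) × 4.5 + f × 0.3 × Ma
- Control-arm variance: 25 + f(1−f)(15−Ma)²
- Treated-arm variance: 25 + f(1−f)[0.7(15−Ma)]², because a 30% reduction shrinks the gap between groups
- SD: square root of the average of the two variances
- Power: noncentral t, 20 per arm, two-sided 0.05

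With f = 0, d = 4.5/5 = 0.90 and power is 79%. The shortfall from 95% at this point comes from the assumed SD, not from the mix.

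The adjusted column keeps SD at 5, that is, with the spread between diagnoses removed.

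| f | Ma | Mean effect | SD, unadjusted week 8 | d | Power, unadjusted | Power, adjusted for diagnosis |
|---|---|---|---|---|---|---|
| 0 | – | 4.50 | 5.00 | 0.90 | 79% | 79% |
| 20% | 8 | 4.08 | 5.55 | 0.73 | 62% | 71% |
| 20% | 6 | 3.96 | 5.89 | 0.67 | 55% | 69% |
| 50% | 8 | 3.45 | 5.84 | 0.59 | 44% | 57% |
| 50% | 6 | 3.15 | 6.33 | 0.50 | 34% | 49% |

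Example, f = 50% and Ma = 6: mean = 0.5 × 4.5 + 0.5 × 1.8 = 3.15. Variances are 25 + 0.25 × 81 = 45.25 and 25 + 0.25 × 39.69 = 34.92. SD = √40.09 = 6.33 and d = 3.15/6.33 = 0.50.

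**3. Starting from the plan's own 95%.** With 4.5 points (30% of 15) and d = 1.14, the implied SD is 4.5/1.14 = 3.95. Take anxiety-only patients at baseline 6 with an effect of 0 or 1.8 points (normal approximation).

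- Dilution of the mean alone, SD unchanged: power 0.82-0.89 at 20% anxiety-only and 0.44-0.71 at 50%.
- With the added spread of unadjusted week-8 scores: 0.65-0.70 at 20% and 0.27-0.44 at 50%.

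**4. Does the variance always rise?** No. On change scores, with the anxiety-only SD between 2 and 3.95, the overall SD is 3.3-4.3 against 3.95. It can fall as well as rise.

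**The case against.** The strongest reply is that the plan makes no false statement here. Every participant completes the PHQ-9, so calling it common to all is correct about administration. It is also offered only as an example, after the plan concedes that several outcomes make a single calculation difficult. That stands, but the example is still the only numerical support for 20 per arm.

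The anxiety-only share, both baselines and the SD are assumptions. The 30% change is not restricted to depressed patients and may already describe a mixed sample. This also stands: the size of the loss cannot be established from the documents.

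The covariate list is open-ended, the article is condensed, and an analysis plan may say more. That is fair. Even so, the covariates are described as demographic, and neither diagnosis nor baseline score is demographic.

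Three stronger readings are tempting but not supported:

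- A reader might infer that PHQ-9 cannot show benefit in anxiety patients. The illustration itself gives them 1.8 to 2.4 points (0.3 × 6 to 0.3 × 8), and GAD-7 is collected from everyone.
- A reader might infer that mixing diagnoses necessarily inflates the variance. Step 4 shows that this depends on the form of the outcome and the adjustment.
- A reader might conclude that a PHQ-9 plus GAD-7 total should be the endpoint. No power has been worked out for it, it could be diluted in its turn by depression-only patients with low GAD-7 scores, and it would change the endpoint after recruitment has begun.

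**Conclusion.** The point holds in a limited form. Eligibility is wider than the condition that the sizing scale measures, 20 per arm leaves no slack because it already needs a standardised difference of about 1.17, and the model as described omits two baseline variables that would recover precision.

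Under the stated assumptions, power at 20 per arm falls from 79% to about 34-62% without adjustment and is about 49-71% with adjustment for diagnosis. Adjustment therefore recovers part of the loss, not all of it, since the smaller mean effect remains. The direction of the dilution rests on some entrants having low baseline PHQ-9 and a correspondingly smaller effect in points. The rise in SD rests further on analysing week-8 scores without baseline or diagnosis. The percentages show plausible size and are not estimates for this trial.

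**What to change.** In Data Analysis:

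1. Add the index diagnosis (depressive, anxiety, both) and the baseline score of the outcome being analysed to the regression covariates.
2. Report the PHQ-9 and GAD-7 effects by index diagnosis descriptively, without subgroup tests.
3. State that the 0.95 power is conditional on the PHQ-9 effect and SD assumed for the mixed depression-or-anxiety sample, and give those values.

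The cost is text only. A psychiatrist confirms each diagnosis and both scales are scored at entry, so no new data are needed. Diagnosis in three categories and one baseline score use three degrees of freedom. With 40 evaluable patients and a model with intercept, arm, age and a two-level gender term, the residual falls from 36 to 33, a small price. Recruitment had begun when the article was written (11 participants), so the change should be dated and made before outcome data are analysed. The endpoint list need not change.
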